## Methods/Design

### Study design and population

A prospective, observational cohort study with a one-year follow-up is currently conducted to determine the clinical effects and impact on the gut microbiota composition of empiric antibiotic use in early life. Infants are recruited from the maternity wards and neonatal wards of four teaching hospitals in the Netherlands: the St. Antonius Hospital in Nieuwegein, the Tergooi Hospital in Blaricum, the Gelre Hospitals in Apeldoorn and the Meander Medical Center in Amersfoort. This study was approved by the joined Medical Ethics Committee (VCMO) of the St Antonius Hospital and Meander Medical Center (nowadays MEC-U: Medical Research Ethics Committees United (Nieuwegein)). In The Netherlands, since 2013 studies only need to be approved by one Ethics Committee. Subsequently, for other participating centers, proof of local feasibility needs to be given. The approved protocol was consequently checked for local feasibility and expertise at Tergooi Hospital and Gelre Hospitals and permission for study implementation was obtained by the respective boards of directors. The study is performed in accordance with the ethical standards laid down in the 1964 Declaration of Helsinki and its later amendments.

All parents of term infants (≥ 36 weeks of gestational age) who stay in the hospital for at least 24 h, are approached for participation in the study.

In total 150 infants, treated with antibiotics because of (a high suspicion of) a perinatal infection during the first week of life, will be recruited. The control group comprises 300 healthy newborns, born in the hospital and needing clinical observation for 24–48 h for several reasons like maternal comorbidity, low probability of neonatal infection, blood sugar monitoring, meconium containing amniotic fluid, or delivery by caesarean section. For a balanced composition of the control group, as much as possible infants that are suspected to have a neonatal infection but for whom watchful waiting is allowed (and no antibiotic treatment has to be started) will be included.

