### Inclusion and exclusion criteria

Inclusion criteriaTerm-born babies (≥ 36 weeks gestational age)(Short) stay on maternal ward or admission to neonatal ward because of antibiotic treatmentSigned informed consent by the parents

Exclusion criteriaCongenital illness or malformationsSevere perinatal infections for which transfer to the neonatal intensive care unit is neededMaternal probiotic use ≤ six weeks before deliveryInsufficient knowledge of the Dutch language.

Infants suspected of neonatal infection will be treated with antibiotics according to the local hospital protocols. All hospitals use gentamycin in combination with either penicillin, amoxicillin or amoxicillin/clavulanic acid. During the study period, type of feeding is closely monitored, as parents monthly report the type of feeding on the calendar list (breast- or formula feeding). Parents are free in their choice of feeding regime, and after six months infants will be on solid food, but not all the infants in the study will have the exact same diet as this is neither feasible nor ethical. Mother’s intake of antibiotics or drugs during pregnancy, delivery and during breastfeeding (if applicable) will be recorded. Delivery/hospital data will be extracted from patient records.

All parents have to give informed consent prior to inclusion in the study. Follow up continues during the first year of life, in which parents collect and store eight fecal samples of their infant. Parents are also asked to collect a fecal sample of their child around the 2^nd^ birthday and they give permission for a possible approach for a follow-up in about 5–6 years.

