### Statistical analysis

We will evaluate the potential relationships between antibiotic use in early life and the various (clinical) endpoints. Variables are verified for normal distribution and *t*-tests will be used for testing the null hypothesis. Either logistic regression analysis or cox regression analysis will be applied to the data (appearance of the primary endpoint(s) will be recorded as specifically as possible), so that odds ratios or hazard ratios and their 95 % confidence interval can be presented for description of the relationships. Multivariate models will be used to assess confounders and confounding effects. We will perform post hoc analyses to look for potential effects of the different antibiotic regimes. Outcomes may, possibly, be classified into subgroups. According to antibiotic treatment after the first two weeks, children will be grouped based on the number of antibiotic courses during the first year of life (0 / 1 / 2 or more courses). Within the ‘treatment groups’ a distinction can be made between the class or spectrum of the prescribed antibiotics.

Microbiota composition will be described by means of abundance, diversity and (dis)similarity. Diversity is calculated using the Shannon index [42] and differences in this index will be tested with Mann–Whitney *U* test. Dissimilarities between samples, or between-sample diversity, are calculated as the cosine distance between each pair of samples and analyzed with principal coordinate analysis (PCoA). All statistical analysis will be conducted using SPSS version 22.0 (SPSS Inc., Chicago, IL, USA) and the vegan software package in R (Foundation for Statistical Computing, Vienna, Austria).

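### Shannon diversity is to be compared by a crude Mann–Whitney test across four hospitals that treat by local protocol, so hospital differences could be mistaken for, or hide, an antibiotic effect

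*Protocol article*

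**What the plan says.** Under Study design and population: "Infants are recruited from the maternity wards and neonatal wards of four teaching hospitals in the Netherlands". The same section gives 150 treated and 300 control infants as study-wide numbers and states no ratio, matching or stratification by hospital. Controls should include "as much as possible infants that are suspected to have a neonatal infection but for whom watchful waiting is allowed".

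Under Inclusion and exclusion criteria: "Infants suspected of neonatal infection will be treated with antibiotics according to the local hospital protocols". The next sentence concerns the drugs: "All hospitals use gentamycin in combination with either penicillin, amoxicillin or amoxicillin/clavulanic acid".

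Under Statistical analysis, clinical endpoints are covered by "Either logistic regression analysis or cox regression analysis will be applied to the data" and "Multivariate models will be used to assess confounders and confounding effects", with no covariate listed. For the Shannon index, "differences in this index will be tested with Mann–Whitney" U. Dissimilarity is handled by principal coordinate analysis, and no group test on the distances is named. Hospital is not mentioned anywhere in that section.

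The Background names mode of delivery and contact with nursing or hospital staff among the factors that shape the infant microbiota. Under Collection of fecal samples, ward nurses take and freeze the first samples.

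**The concern.** Hospital can be tied to exposure, because treatment follows local protocols and nothing in the design equalises the treated share across sites. It can also be tied to the microbiota, by the article's own list of influences. A factor linked to both confounds a crude comparison.

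For diversity, the named test fixes the problem in place. A Mann–Whitney U test compares two pooled groups and cannot hold hospital constant, so a covariate list kept in another document would not repair it; the test itself has to change. The article puts the microbiota comparison before the clinical outcomes in its Aims, and diversity is one of three descriptions of composition it plans. A difference between hospitals could then be reported as a difference between treated and untreated infants, or could cancel a real one.

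**Working it through.** **1. The plan's own figure.** Inputs from Power calculation: eczema 35% vs 20%, 1:2 allocation, 80% power, alpha 5% (two-sided assumed, as sidedness is not stated), 15% dropout.

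- Pooled rate: (0.35 + 2 × 0.20)/3 = 0.25.
- n treated = [1.96 × √(1.5 × 0.25 × 0.75) + 0.8416 × √(0.35 × 0.65 + 0.20 × 0.80/2)]² / 0.15² = (1.039 + 0.467)² / 0.0225 ≈ 101.
- Total: 101 + 202 = 303 completers; 303/0.85 ≈ 357 enrolled (392 with continuity correction).

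The stated 450 is larger than its inputs require, which is an error in the safe direction and does not bear on this point. At 450 less 15% (127.5 and 255 completers), power is 88.1%. That is the baseline for step 4.

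**2. Size of the possible bias.** The documents give no hospital-specific figures. Assumed: four equal hospitals, one third treated overall, no true effect within any hospital, and treated share s and outcome level r both rising in the same order across hospitals, which is unfavourable.

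Crude treated level = Σ s·r / Σ s. Crude control level = Σ (1 − s)·r / Σ (1 − s).

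Example with shares 13.3/26.7/40.0/53.3% and eczema risks 10/16.7/23.3/30%:

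- Treated: (1.33 + 4.45 + 9.33 + 16.00)/1.333 = 23.3%.
- Control: (8.67 + 12.22 + 14.00 + 14.00)/2.667 = 18.3%.
- Spurious difference: 5.0 points.

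Rejection rates below are for a crude two-sided two-proportion test at 127.5 and 255 completers, nominal 5%.

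| Treated shares | Outcome levels | Treated vs control | Difference (points) | Odds ratio | Rejection |
|---|---|---|---|---|---|
| equal | any | 20.0 vs 20.0% | 0 | 1.00 | 5% |
| 23–43% | 15–25% | 20.8 vs 19.6% | 1.3 | 1.08 | 6% |
| 13–53% | 15–25% | 21.7 vs 19.2% | 2.5 | 1.17 | 9% |
| 13–53% | 10–30% | 23.3 vs 18.3% | 5.0 | 1.36 | 22% |
| 5–62% | 10–30% | 24.9 vs 17.5% | 7.4 | 1.56 | 40% |

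Differences are taken before rounding. Equal outcome levels with unequal shares also give zero bias and 5% rejection.

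**3. Carrying this to diversity.** The same weighted means apply to a mean Shannon index. Dividing the spurious difference by the spread between the lowest and highest hospital gives the fraction absorbed: 1.25/10 = 12.5% for shares of 23–43%, 5.0/20 = 25% for 13–53%, and 7.4/20 = 37% for 5–62%. The spread in diversity between the hospitals is not given, so no rejection rate for the Mann–Whitney test is claimed.

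**4. Cost of adjusting.** The share of treatment variance explained by hospital is R² = Var(s)/[(1/3)(2/3)]. For shares of 13–53%, Var(s) = (2 × 0.2² + 2 × 0.0667²)/4 = 0.0222, so R² = 0.0222/0.2222 = 0.10. Multiplying the completers by (1 − R²) gives the power for eczema 35% vs 20%:

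| Treated shares | R² | Power with hospital term |
|---|---|---|
| equal | 0 | 88.1% |
| 23–43% | 0.025 | 87.3% |
| 13–53% | 0.10 | 84.7% |
| 5–62% | 0.221 | 79.4% |

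**The case against.** The strongest objection is that the article does plan adjustment. It commits to logistic or Cox regression and to multivariate models for confounders, and it lists no covariates at all, so hospital is not singled out for omission. A covariate list is ordinarily left to the full protocol or the analysis plan. This stands for the clinical endpoints: a reader might infer that the eczema comparison has no hospital term, but the text shows only that hospital is unnamed. It does not answer the point on the Mann–Whitney test, which has no place for a covariate.

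Three further readings are tempting and unsupported.

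- A reader might take the local-protocol sentence to show that the threshold for treating differs between hospitals. The sentence that follows it is about drug combinations, so it can equally concern regimen, and nothing in the article compares thresholds. If regimen does follow hospital, the planned "We will perform post hoc analyses to look for potential effects of the different antibiotic regimes" would be exposed too, but that is a different comparison.
- A reader might suppose that diagnosis coding or prescribing, which define an eczema case, vary by hospital. The article describes a standard classification with a pharmacy check and reports no such variation.
- A reader might conclude that bias is certain. It needs both the treated share and the outcome level to vary by hospital in a related way, and the article gives neither. Controls come from the same four Dutch teaching hospitals.

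The rejection rates above also belong to a crude test of proportions that the article does not name, under an unfavourable ordering. Even the largest spurious difference, 7.4 points, is about half the 15-point design difference.

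**Conclusion.** The point holds for the microbiota comparison and in conditional form. The treated share may differ by hospital, the article itself names hospital-related influences on the microbiota, and the one test named for diversity cannot adjust for hospital. Hospital differences could therefore be mistaken for an antibiotic effect or conceal one.

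Under the assumed shares, 12.5% to 37% of the spread between hospitals would pass into the crude difference. If either the treated share or the outcome level is the same across hospitals, nothing passes. For the clinical endpoints the finding is only that hospital should be named among the covariates of models already planned. It is worth acting on because hospital is known for every infant and the remedy is cheap, not because bias has been shown.

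**What to change.** - Replace the crude Mann–Whitney test of Shannon diversity with a hospital-stratified rank test (for example van Elteren) or a regression with hospital as a fixed factor.
- If a distance-based group test accompanies the principal coordinate analysis, restrict its permutations within hospital.
- Name hospital among the covariates of the planned logistic or Cox models.
- Report treated and control numbers per hospital, so that readers can judge how far exposure and hospital overlap.

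The cost is a change of analysis wording, three degrees of freedom, and the power loss in step 4: about 1 to 3 percentage points on the eczema comparison under mild to moderate imbalance, and about 9 (88.1% to 79.4%) if treated shares differ widely. No new data are needed, and recruitment need not change. Adjusting for hospital does not remove the separate limitation, acknowledged in the Discussion, that treated infants may differ from healthy ones.

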**Methods/Design:**

450 term born infants, of whom 150 are exposed to antibiotic treatment in early life and 300 are not (control group), are included in this observational cohort study with a one-year follow-up. Clinical outcomes, including coughing, wheezing, fever >38 °C, runny nose, glue ear, rash, diarrhea and >3 crying hours a day, are recorded daily by parents and examined by previously defined doctor’s diagnosis. A blood sample is taken at closure to investigate the infant’s vaccination response and sensitization for food and inhalant allergens. Fecal samples are obtained at eight time points during the first year of life. Potential differences in microbial profiles of infants treated with antibiotics versus healthy controls will be determined by use of 16S-23S rRNA gene analysis (IS-pro). Microbiota composition will be described by means of abundance, diversity and (dis)similarity. Diversity is calculated using the Shannon index. Dissimilarities between samples are calculated as the cosine distance between each pair of samples and analyzed with principal coordinate analysis. Clinical variables and possible associations are assessed by appropriate statistics.

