Relatively few studies have determined the direct effects of antibiotics on the composition of gut microbiota and/or addressed the mechanisms underlying this association [13, 29, 34]. Initial studies were based on culture-dependent techniques, but altered intestinal microbiota in antibiotic treated infants could already be identified by these relatively limited techniques [35, 36]. In the last few years, the development of culture-independent (molecular) approaches for studying the intestinal microbiota composition has changed and advanced our original perspective and insight into the impact of the composition of the microbiome [37, 38]. By using molecular fingerprinting and determination of 16S rRNA genes (by quantitative polymerase chain reaction, qPCR), overgrowth of *Enterococci* and arrested growth of *Bifidobacterium* in infants exposed to antibiotics in the first week of life has been described [34].

Overall, evidence is growing that an aberrant microbiota composition as a result of antibiotic treatment can have clinical effects, but more robust studies are needed with a higher number of patients to elucidate the exact effects of antibiotics on the developing microbiota and its association with health in the first year of life. This study therefore aims to investigate the potential clinical and microbial consequences of empiric antibiotic use in early life by following a large cohort of 150 treated and 300 untreated infants and compare them with respect to their health status as well as their developing gut microbiota.

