**Fig. 1 Fig1:**
[figure not shown]
Overview of the sample time points and outcomes

Potential differences in proportions (abundance and diversity) of intestinal bacterial groups (phyla) and species in antibiotic treated infants versus healthy controls will be determined by use of 16S-23S rRNA gene analysis. Secondly, we investigate differences in clinical outcomes between infants treated with antibiotics and controls. We evaluate incidences of atopic dermatitis (eczema), food allergy, upper respiratory tract infections (URTI), lower respiratory tract infections (LRTI), gastrointestinal infections (GITI) and excessive crying, prospectively assessed by parental reports and retrospectively assessed by doctor’s diagnoses. The clinical endpoints will be linked to the developing intestinal microbiota during the first year of life. Body mass index and standard deviation (SD)-scores are calculated from individual weight and height curves.

Parents of all included infants will report the use of antibiotics (type of antibiotics and duration of treatment) during the complete study period (i.e. the first year of life) on the calendar lists. Moreover, (the type of) prescribed antibiotics will be investigated at the end of the initial study period by approaching the infant’s pharmacy on medications used in the first year of life. Parents are also asked to report the moment of stool collection (date) on the collection vial, so the investigators can calculate the time between antibiotic treatment and stool sample collection. We hypothesize that in early life antibiotic treated infants develop more eczema during their first year than non-antibiotic treated infants (healthy controls). We also expect an increase in incidence of (parental reported as well as doctor’s diagnosed) food allergy, respiratory tract infections (RTI’s) and gastrointestinal tract infections (GITI’s) in infants treated with antibiotics compared to controls.

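### Maternal antibiotics are recorded but enter neither the exposure groupings nor the named diversity test, so the early microbiota contrast can mix maternal exposure with the infant's own treatment

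*Protocol article*

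**What the plan says.** **Groups.** The exposed group is 150 infants "treated with antibiotics because of (a high suspicion of) a perinatal infection during the first week of life" (Study design and population). For the controls, the same section says: "The control group comprises 300 healthy newborns, born in the hospital and needing clinical observation for 24–48 h for several reasons like maternal comorbidity"; the listed reasons also include "meconium containing amniotic fluid, or delivery by caesarean section". As far as possible, controls are to include "infants that are suspected to have a neonatal infection but for whom watchful waiting is allowed". Group membership therefore depends on what the infant received. The Background states the objective in the same terms, "by following a large cohort of 150 treated and 300 untreated infants".

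**Maternal exposure.** The mother's "intake of antibiotics or drugs during pregnancy, delivery and during breastfeeding (if applicable) will be recorded" (Inclusion and exclusion criteria). The baseline questionnaire also asks about medication in pregnancy and delivery (Outcomes). The only maternal intake among the exclusion criteria is probiotic use in the six weeks before delivery.

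**Analysis.** The Statistical analysis section plans logistic or Cox regression for the clinical endpoints and multivariate models for confounding, without naming covariates. It sub-classifies antibiotics by regimen, by number of later courses (0, 1, 2 or more) and by class or spectrum. All of these describe the infant's treatment. The Shannon index is to be compared by Mann–Whitney U, and between-sample dissimilarity by cosine distance and principal coordinates.

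**The concern.** The study attributes differences in microbiota and health to empiric treatment of the infant. The article itself treats the mother as a source of the infant's flora: maternal stool and parental swabs are taken to study transmission, and maternal probiotics are an exclusion. Maternal antibiotics around delivery are thus a plausible second influence on the same outcome. They may go with the reason for treating the infant, since suspected perinatal infection concerns mother and child together.

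If the share of exposed mothers differs between groups, an unadjusted comparison credits part of the maternal effect to the infant's treatment, or hides part of the treatment effect. This is most plausible in the early samples (T1 to T4: day one, day two, one week, two weeks). Exposure in late pregnancy or at delivery precedes all of these, while the infant's own course may start at any time in the first week.

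**Working it through.** **1. Which planned analysis can separate maternal exposure?**
- Clinical endpoints: regression with multivariate models. Maternal antibiotics can be entered, although the article does not say so.
- Antibiotic sub-groupings: regimen, later courses, class or spectrum. Maternal exposure is in none of them.
- Shannon index: two-group Mann–Whitney U. No covariate can be entered.

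As written, the gap is clearest for diversity.

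**2. Inputs.** From the Power calculation section: eczema 20% in controls and 35% in treated infants, 150 and 300 infants, 15% dropout, hence 0.85 × 150 = 127.5 and 0.85 × 300 = 255 completers. Assumed, because no document gives them: the share of exposed mothers among treated infants (g) and controls (f), and the added eczema risk from maternal exposure (a).

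**3. The plan's own figure.** For 20% versus 35%, 1:2 allocation, 80% power and two-sided 5%, the usual formula gives 101 + 202 = 303, or 3 × 119 = 357 after 15% dropout (393 with continuity correction). The stated 450 is larger. At 127.5 and 255 completers, power is about 88% (about 85% with the correction). This is a separate, conservative matter; here it only shows that there is some slack.

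**4. Size for a clinical endpoint.** With an additive maternal effect,

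observed difference = 15 + a × (g − f) points.

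| Assumed g, f, a | Maternal part (points) | Observed difference |
|---|---|---|
| 30%, 30%, any a | 0 | 15 |
| 60%, 30%, 7.5 | 0.30 × 7.5 = +2.25 | 17.25 |
| 70%, 30%, 10 | 0.40 × 10 = +4 | 19 |
| 0%, 30%, 7.5 | −0.30 × 7.5 = −2.25 | 12.75 |
| 0%, 30%, 15 | −0.30 × 15 = −4.5 | 10.5 |

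In the third row, if the infant's treatment had no effect at all, the spurious 4 points would give a significant result in the expected direction about 14% of the time. The last two rows are an extreme case, with exposure in controls and none in treated infants; power would be 75.1% and 57.6%. The sign follows g − f, which the documents do not give.

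**5. Size for diversity.** Let maternal exposure shift the Shannon index by d standard deviations. The group means then differ by d × (g − f) for that reason alone. With all 150 and 300 samples, the standard error of a mean difference is √(1/150 + 1/300) = 0.10 SD. At g − f = 0.30 the shift is 0.30d / 0.10 = 3d standard errors, so a maternal effect of one third of an SD moves the comparison by one standard error. This uses means as a guide to the rank test.

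**6. Restricting controls only.** With g = 60%, f = 30% and a = 7.5, the maternal part is 2.25 points. Dropping exposed mothers from controls alone makes f = 0, and the maternal part becomes 0.60 × 7.5 = 4.5 points, which is double.

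**7. Restricting both groups.** The maternal part is then zero, at a cost in precision. The 95% half-width is 1.96 × √(0.35 × 0.65/n₁ + 0.20 × 0.80/n₂):
- n₁ = 127.5, n₂ = 255 (no restriction): 9.6 points.
- 30% removed from each group, n₁ = 89.25, n₂ = 178.5: 11.5 points.
- 60% and 30% removed, n₁ = 51, n₂ = 178.5: 14.3 points.

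**The case against.** **The controls are what the objective asks for.** The hypothesis is that treated infants "develop more eczema during their first year than non-antibiotic treated infants (healthy controls"). An untreated infant whose mother had antibiotics meets that definition. A reader might infer that the reference group is contaminated, or that eligibility is at fault because mothers are screened for probiotics and not for antibiotics. The documents do not support this. Excluding one maternal exposure does not oblige the study to exclude another, and recruiting watched infants with suspected infection is a deliberate step towards comparability. This objection stands in full.

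**Confounding is already provided for.** Maternal antibiotics are recorded and multivariate models are planned; the Discussion concedes that treated and healthy infants may differ. A condensed article may leave the covariate list to a fuller document. This stands for the clinical endpoints: an unnamed covariate there is no error. It does not reach the Shannon comparison, where the article does name a test and that test cannot adjust. Nor does it reach the sub-groupings, which the article spells out without the mother.

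**The size is assumed.** This stands. No document gives the share of exposed mothers or their effect, or says that the listed reasons for observation involve maternal antibiotics. The 20% control rate is taken from general prevalence, not from a strictly unexposed group. Equal shares with an additive effect leave the 15 points unchanged.

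**Conclusion.** The point holds as a matter of analysis, not of eligibility. Maternal antibiotics are a recorded co-exposure, possible in both groups, which the article puts to no use in its groupings or in its named diversity test. If their frequency differs between groups, that comparison mixes two exposures, and the early samples are the most open to it.

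Neither direction nor size can be fixed from the documents. Under the shares assumed above, the maternal part of the eczema difference runs from −4.5 to +4 points, and is zero when shares are equal and effects additive. A reader might infer that the antibiotic effect will be diluted; that requires exposure to be more frequent among control mothers, which nothing in the article states. This is an inexpensive improvement worth making and does not invalidate the design.

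**What to change.** Leave enrolment and the two groups as they are. In the analysis plan:

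1. Classify every infant, treated and control, by maternal antibiotics in late pregnancy or delivery (yes/no), with the window stated. Exposure through breastfeeding can begin after the groups are formed, so describe it rather than build it into this baseline variable.
2. Report the shares by group. They decide whether the issue matters in practice.
3. Use the variable as a covariate or stratum in the treated-versus-control comparison of clinical endpoints and microbiota. For the Shannon index, replace the plain Mann–Whitney U with a stratified rank test (van Elteren) or a regression of the index on treatment and maternal exposure.
4. Add a sensitivity analysis that excludes maternally exposed infants from both groups, not from controls only, and describe maternally exposed controls separately.

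The data are already collected, so the change is one of wording and analysis. Adjusted intervals will be somewhat wider. The restricted analysis is smaller and, depending on the shares, may be clearly less precise, which is why it belongs as a sensitivity analysis. If nearly all mothers in one group prove to be exposed, one stratum will be thin and the report should say so.
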